## Abstract

**Background:** Incidence and mortality from cervical cancer have remained high due to many obstacles facing the implementation of organized screening programs in resource-constrained countries such as Nigeria. The application of mobile technologies (mHealth) to health services delivery has the potential to reduce inequalities, empower patients to control their health, and improve the cost-effectiveness of health care delivery.

**Aim:** To assess the efficacy of mobile technology intervention on Pap test screening adherence compared to a control condition and also determine the factors affecting the uptake of Pap smear screening practices among women in Lagos.

**Methods:** This is a multi-center randomized controlled trial that will involve women aged 25 to 65 years attending the General Outpatient clinics of the two tertiary health institutions in Lagos, Nigeria between April and December 2020. At baseline, a total of 200 National Health Insurance Scheme (NHIS) enrollees will be randomized to either a text message arm or usual care (control) arm. The primary outcome is the completion of a Pap smear within 6 months of enrolment in the study. The associations between any two groups of continuous variables will be tested using the independent sample t-test (normal distribution) or the Mann-Whitney U test (skewed data) and that of two groups of categorical variables with Chi-square
*X
^2^*or Fisher's exact test where appropriate. Using binary logistic regression model, we will adjust for age and other relevant sociodemographic and clinical variables and adherence to Pap test screening. Statistical significance will be defined as
*P*-value less than 0.05.

**Discussion: **The mHealth-Cervix study will evaluate the impact of mobile technologies on cervical cancer screening practices in Lagos, Nigeria as a way of contributing to the reduction in the wide disparities in cervical cancer incidence through early detection facilitated using health promotion to improve Pap smear screening adherence.

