### Participants’ enrollment and data collection

Investigators will identify eligible women from the GOP clinics of the two study sites on each day of the study period after which a 20–30 minutes educational health talk on cervical cancer and its prevention is given to these women by the clinic midwives with the assistance of the clinics’ health care teams as part of their usual standard of care. Eligible women are then invited by the investigators to give consent for participation in the clinical trial upon explanation of the purpose and nature of the study. Once consent is obtained, an interviewer-administered questionnaire (see extended data
^17^) is then used to obtain baseline information on sociodemographic variables, cell-phone use, and distance of participants’ residence from the clinics (measured in kilometer using the Google maps). Each woman will receive an estimated $5 credit charge on their cellphones as a token to enable the investigators to keep their phone numbers for as long as the intervention lasts. The women in both arms are each given the complementary card containing the cell-phone number of the cytology clinic coordinators (who are also part of the study) and are subsequently scheduled for 6-month follow-up appointments from their dates of study enrolment. After follow-up, data will be collected from each woman on completion of Pap test screening, the number of GOP clinics attended, the interval from enrollment to date of Pap smear testing and functionality of cell-phone during the same follow-up period (that is, if the cell-phone was in use for at least 5 out the 6 months follow-up or not).

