### Study endpoints

Primary endpoint – This is the completion of a Pap smear within 6 months of enrollment in the study. Participants will be tracked via medical record review as well as through phone calls at 6-month after their enrolment.

Secondary endpoint – This is an assessment of the various factors affecting Pap smear uptake or adherence within 6-month of enrollment among the participating women.

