### Statistical methods

Sample size – We calculated sample size using
G*Power for Windows version 3.1.9.2 (Kiel University, Germany). Using data from our published study
^6^, we estimated the proportion of Pap smear adherence to be approximately 23% for the usual care (control) arm and 60% for the text message (intervention) arm. This is powered for a two-sided test with a Type I error rate of 5% and 80% power, i.e. Zα=1.96 and Zβ=0.84, adjusted for a 10% attrition rate. Therefore, the power calculations will be based on a sample size of 100 in each of the two study arms (making a total sample size of 200).

Statistical analysis – The intention-to-treat principle will be used in the final analyses. Statistical analyses will be carried out using
SPSS version 23.0 for Windows (Armonk, NY: IBM Corp.). Pap smear adherence will be coded as a binary variable. The intervention will be evaluated based only on Pap smear completion at 6-month after the enrollment and baseline survey. The associations between any two groups of continuous variables will be tested using the independent sample t-test (normal distribution) or the Mann-Whitney U test (skewed data) and that of two groups of categorical variables with Chi-square (
*χ*
^2^) or Fisher's exact test where appropriate. Using binary logistic regression analysis, we will adjust for age, socioeconomic class, parity, marital status, number of GOP clinic attendance, the distance of residence from the clinics, interval from enrollment to date of Pap smear testing, the functionality of cellphones and other relevant demographic and clinical variables. Statistical significance will be defined as
*P*-value less than 0.05.

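### The logistic model for Pap smear completion adjusts for follow-up variables, one of which (interval to Pap smear) exists only for women who had the smear, so the model as listed cannot be estimated

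*Protocol article*

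**What the plan says.** The primary endpoint in the protocol article's Study endpoints section reads: "This is the completion of a Pap smear within 6 months of enrollment in the study". Under Statistical methods, "Pap smear adherence will be coded as a binary variable", and this is the only outcome named for the analysis.

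The same section then gives the model: "Using binary logistic regression analysis, we will adjust for age, socioeconomic class, parity, marital status, number of GOP clinic attendance". The stretch of the list at issue is "number of GOP clinic attendance, the distance of residence from the clinics, interval from enrollment to date of Pap smear testing, the functionality of cellphones", after which the list is left open to further demographic and clinical variables.

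The section on enrollment and data collection dates these variables. "After follow-up, data will be collected from each woman on completion of Pap test screening, the number of GOP clinics attended"; the same sentence adds "the interval from enrollment to date of Pap smear testing and functionality of cell-phone during the same follow-up period". Distance of residence, by contrast, is obtained with the baseline questionnaire. The Randomization section places allocation right after the baseline assessment. Visits, interval and phone functionality are therefore all measured after randomisation.

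Statistical methods also commits to intention to treat, says the intervention is judged on 6-month completion alone, and lists chi-square or Fisher's exact tests for comparing two groups on categorical variables. It does not say whether the logistic model serves the arm comparison or the secondary endpoint, which concerns factors affecting uptake.

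**The concern.** A covariate must have a value for women with and without the outcome. The time from enrolment to the smear does not: a woman who never had a smear has no such date. Knowing that an interval exists is the same as knowing that the outcome is yes. A model containing it has nothing left to explain and no usable estimate for arm or for any other factor.

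Visits and phone functionality raise a different and milder issue. Both have values for completers and non-completers alike, so the model can be fitted with them. But a variable that the messages may change is not a proper adjustment variable for the effect of being assigned to messages.

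The only adjusted analysis that the article specifies is at stake. If analysts discover the failure with data in hand and then drop covariates until the model fits, the reported adjusted result will have been chosen after the fact.

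**Working it through.** The plan gives no figure for the adjusted model, so there is none to reproduce. The inputs are the planning completion rates (23% control, 60% intervention), 100 women per arm and 10% attrition, all from Statistical methods.

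**1. Who has an interval.**
- Completers: 0.23 × 100 + 0.60 × 100 = 23 + 60 = 83.
- Non-completers: 77 + 40 = 117.
- With 10% attrition (90 per arm), completers are 20.7 + 54.0 = 74.7 and non-completers 180 − 74.7 = 105.3.

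The counts depend on these rates. The failures in steps 2 and 3 do not.

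**2. Complete-case fit.** All 117 women without an interval drop out. The remaining 83 all have Y = 1. The log-likelihood is Σ log pᵢ, which rises towards 0 as the intercept grows, whatever the arm coefficient. There is no finite maximum, and the arm effect is not identified.

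**3. Filler value at 6 months.** Let T be the interval and c the filler given to non-completers, with every completer at T < c. Choose c′ between the largest completer interval and c. The linear predictor b(c′ − T) with b > 0 is positive for every completer and negative for every non-completer. As b grows, the log-likelihood goes to 0 for any fixed arm coefficient. This is perfect separation, and again the arm effect is not identified. If some completers fall exactly on c, separation is quasi-complete and the interval coefficient still has no finite estimate. Any other filler would be an invented date, and the article provides for none.

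**4. Simulation check.** 500 trials were simulated at 23% and 60% with 100 per arm, completers' intervals uniform on 5 to 182 days, and a filler of 183 days.
- Mean number of women with an interval: 83.1.
- Complete-case outcome constant: 500 of 500 trials.
- Perfect separation with the filler: 500 of 500 trials.

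A single test fit with the filler returned an arm log-odds ratio of −13.9 with a standard error of about 1.1 million. That is an artefact of separation. The unadjusted odds ratio implied by the planning rates is (0.60/0.40) ÷ (0.23/0.77) = 5.02.

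**5. Visits and phone functionality.** No figure can be derived from the documents. The section describing the two arms says that the messages encourage screening and that control women may book a smear in person at the GOP or Cytology clinic. A path from messages to visits to smear is therefore plausible. If it exists, holding visits fixed removes that part of the effect of assignment. But the messages give details of the Cytology clinic, not the GOP clinic, and visits and uptake may share causes such as health-seeking habit. The size and direction of the net shift are therefore unknown.

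**The case against.** The strongest reply is that the logistic model may not carry the primary conclusion. The article says the intervention is judged on 6-month completion under intention to treat and lists chi-square or Fisher tests. That comparison uses none of these covariates. Its power at the planning rates with 90 women per arm is Φ[(0.37 − 1.96 × 0.0735) / 0.0681] = Φ(3.32), about 99.95%. Here 0.0735 is the pooled standard error, √(2 × 0.415 × 0.585 / 90), and 0.0681 the unpooled one, √[(0.23 × 0.77 + 0.60 × 0.40) / 90]. The covariate list also suits the secondary endpoint on factors affecting uptake. All of this stands. It limits the reach of the point but does not rescue the interval, which cannot predict completion in either role.

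A reader might go further than the documents allow in four ways.
- **That the trial could not estimate the effect, or would report a working intervention as ineffective.** This would require the adjusted model to override the unadjusted test, and the article does not say so.
- **That the plan adjusts for its own outcome.** The abstract says "we will adjust for age and other relevant sociodemographic and clinical variables and adherence to Pap test screening". Taken literally this includes the outcome, but the full covariate list does not contain it, and the sentence reads as a drafting slip.
- **That adjusting for visits or phone functionality in itself breaks intention to treat.** Women are still analysed as assigned. Dropping the non-completers is what would exclude randomised women.
- **That the loss from adjusting for visits can be quantified.** Any figure would rest on invented effects of messages on visits and of visits on uptake.

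**Conclusion.** The point holds for the logistic model as listed. The interval from enrolment to Pap smear makes that model inestimable, whether women without a value are dropped (117 of 200 at the planning rates) or given a 6-month filler. This follows from the definition of the variable and needs no assumption about the effect of the messages; the planning rates enter only through the counts.

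The number of GOP visits and phone functionality are post-randomisation variables that do not belong in an adjusted estimate of the arm effect. Any harm from including them depends on whether the messages change them, which the documents do not show.

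The unadjusted comparison by arm is sound, so the fault lies in the adjusted analysis and in the lack of a stated role for it, not in the trial's ability to answer its question. The plan is nevertheless wrong as written, and the text should be corrected.

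**What to change.** - Remove the interval to Pap smear from every logistic model of completion, including any model for factors affecting uptake.
- Name the comparison of 6-month completion by assigned arm, in all randomised women, as the primary analysis, and say which aim the logistic model serves.
- Restrict any adjusted estimate of the arm effect to the baseline covariates already listed: age, socioeconomic class, parity, marital status and distance of residence.
- Report GOP visits and phone functionality by arm as process measures.
- If the interval is analysed, treat it as a time-to-event outcome with non-completers censored at 6 months.
- Reword the abstract's sentence on adjustment to match.

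The cost is a change of wording, with no new data and no change to the sample size. The Study status section says recruitment had not begun when the manuscript was first submitted. The change is best made before any outcome data are seen and notified by the route that the protocol sets for important modifications.

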### Quality control and data monitoring

All investigators and research assistants will be required to undergo training before the trial to guarantee consistent practice. The training will include an understanding of inclusion/exclusion criteria, follow-up procedures, and completion of the questionnaire. Identifiable data will be transferred to an electronic database system located in a guarded facility at the trial site by the research assistant. Access to identifiable data is restricted only to the PI during and after the trial completion. The trial will be monitored by quality assurance personnel from the research management office of the College of Medicine, University of Lagos, who will be independent of the study team, and an independent steering committee. There will be periodic monitoring to guarantee accuracy and quality throughout the study period. The essential documents (consent information, enrolment, protocol deviations, and losses to follow-up) will be monitored and checked for accuracy and completeness by the monitors. The principal investigator ([name]) is responsible for the overall project and for organizing steering committee meetings. The independent steering committee will be responsible for ensuring the overall safety of participants, coordinating study meetings, supervising the study, monitoring data safety, and overseeing quality control.

### Ethics

This study protocol was approved by the Health Research Ethics Committee of College of Medicine, University of Lagos (CMUL HREC) on 2
^nd^ February 2020 with approval number CMUL/HREC/12/19/704. Participants will provide written informed consent before their participation in the trial and the participant will keep a signed copy of the consent form for future references.

### Dissemination of information

The trial will be reported in line with the Consolidated Standards of Reporting Trials (CONSORT) checklist and the results will be disseminated in peer-review scientific journals. Important modifications to the trial protocol will be communicated to the funder, study investigators, CMUL HREC, trial participants and trial registries.

### Study status

At the time of initial manuscript submission, recruitment is yet to commence into the trial. Participants’ enrolment will start in May 2020, and the last woman is expected to be included in the trial in July 2020. The manuscript reports protocol version 3.0 (30
^th^ March 2020).

## Discussion

Cervical cancer is a major public health disease in Nigeria. However, screening is still not a national priority as only 23% of adult females has ever been screened
^6^. There is wide use of mobile technologies in Nigeria and most parts of sub-Saharan Africa, but there are currently no randomized controlled trials that have described the use of these technologies for cancer screening. This protocol describes a randomised controlled trial of a novel intervention (mHealth technologies using text messages) to improve Pap smear screening adherence among women in Lagos. The mHealth-Cervix study will evaluate the impact of mobile technologies on cervical cancer screening practices in Lagos, Nigeria and determine the factors that affect this screening adherence as a means of reducing the disparities in the incidence of cervical cancer through early detection facilitated using health promotion to improve Pap smear screening adherence. If found to be effective in increasing adherence to screening, the mHealth intervention strategy may become an important tool for reducing the cervical cancer burden, and its associated morbidity and mortality. This could also be applied in the future for the health promotion and prevention of other major disease conditions.

## Data availability

### Underlying data

No data are associated with this article

### Extended data

Harvard Dataverse: Replication Data for: Impact of mobile technologies on cervical cancer screening practices in Lagos, Nigeria (mHealth-Cervix): Protocol for a randomised controlled trial
https://doi.org/10.7910/DVN/GXE1ON
^17^

*This trial protocol contains the following underlying data:*

*Consent form.pdf (Study consent form)*

*Questionnaire_f1000.docx*

### Reporting guidelines

SPIRIT checklist for “Impact of mobile technologies on cervical cancer screening practices in Lagos, Nigeria (mHealth-Cervix): Protocol for a randomised controlled trial”
https://doi.org/10.7910/DVN/GXE1ON
^17^

Data are available under the terms of the
Creative Commons Zero "No rights reserved" data waiver (CC0 1.0 Public domain dedication).
